## Abstract

**Background:**

Convergence insufficiency is a common issue in the field of binocular vision. Various treatment options have been suggested for managing this condition, but their efficacy in individuals with presbyopia remains unclear. The objective of this study is to compare the effectiveness of home-based vision therapy and prism prescription, in presbyopic patients with convergence insufficiency.

**Methods/design:**

It is a randomized, prospective, double-blind clinical trial, with total of 150 participants randomly assigned to the three groups. The Control Group will receive a new near glasses as a conventional prescription, along with aimless and random eye movement exercises that do not have any convergence or accommodation effects. The Home Vision Therapy Group will receive new near glasses with accommodative and convergence eye exercises. The Prism Group will receive a near prismatic glasses prescribed using the Sheard’s criterion. All treatments will be administered for a period of 2 months, and measurements of the modified convergence insufficiency symptoms survey (CISS), near point convergence, near phoria, and positive fusional vergence will be taken at baseline, one month later, and at the end of the treatment.

**Discussion:**

We aim to identify which component - either the prism prescription or the home vision therapy - is more effective in improving binocular abilities and reducing patients’ symptom scores.

**Trial registration:**

ClinicalTrials.gov NCT05311917 with last update on 04/22/2023.

## Background

Convergence insufficiency (CI) is a binocular vision problem characterized by an excess of exophoria in near activities compared to distance, moreover, its includes remoted near point of convergence (NPC) and decreased positive fusional vergence (PFV) [1]. Its prevalence typically ranges from 2.25 to 17.6%, depending on the population studied and the criteria used to define it [2–5]. This problem is also frequently observed in individuals with presbyopia with prevalence of 29.6% [4]. The most common ocular finding in these patients is an increase in near exophoria, which can impair performance in activities such as reading, computer work, and other near tasks [6]. Symptoms of CI include difficulty seeing at close range, headaches, eye pain during reading or studying, blurred vision, diplopia, movement of words while reading, a feeling of pressure in the eyes, and difficulty concentrating. Signs of it include an increasing near point of convergence, more exophoria at near than distance, a decreased AC/A ratio, and a decreased positive fusional vergence [7] and the convergence insufficiency symptom survey (CISS) questionnaire is the initial standardized and valid tool used to evaluate the frequency and nature of symptoms in patients with CI [8, 9]. Vision therapy is typically considered as the primary treatment option for CI, with base in prism prescription being an alternative choice [6]. However, given the age-related changes in the interaction and functioning of the accommodation and convergence systems, it is crucial to study how these systems interact in elderly individuals [7]. It is also important to compare the responses of these age groups to vision therapy and base in prism prescription [10]. While vision therapy has proven effective in reducing symptoms and enhancing visual function in patients with CI, the different accommodation and vergence systems in elderly individuals may yield different results [11]. There is little information about CI in presbyopic subjects, to our knowledge, in these patients, only one study investigated vision therapy [12] and base in prism prescription in which prism proved superior albeit in a very small sample of participants [13].; also patients age can impact the vision therapy compliance [14] and the documentation of effectiveness of vision therapy and base in prism prescription in presbyopic individuals with convergence insufficiency is insufficient.

## Methods/design

### Objectives of the study

The primary objective of this 3-parellel arm RCT is to assess the efficacy of home-based vision therapy and base in prism prescription in improvement of NPC and PFV, in presbyopic individuals who have CI. Three comparisons will be made: differentiation of the home vision therapy from base in prism prescription, and differentiation of home vision therapy from control group, differentiation of base in prism prescription from control group. Additionally, as secondary objectives, the study will involve a subjective evaluation of the clinical significance of any differences observed among groups and before and after of the interventions, using modified CISS questionnaire. We considered that a minimum variation of, 4 cm, 4 prism diopter, 6 prism diopter, and 6 points are necessary for clinically significant treatments for NPC, phoria, positive fusional vergence, and CISS score. In phase 1 we modified the CISS for elderly subjects. For this purpose, we added “Using your near optical correction” before each item and we assessed validity and reliability of the questionnaire using classical and modern analysis. Ten specialist experts in binocular vision were invited to evaluate the survey’s relevancy, clarity, simplicity, content validity ratio, and face validity. The modified CISS-P were completed twice by 50 presbyopic individuals with convergence insufficiency (CI) and 50 presbyopic individuals with normal binocular vision. Interclass correlation coefficient (ICC) for the instrument and each item were computed to assess test-retest reliability. Also we used the jMetrik software to conduct Rasch analysis. The CISS were adopted for presbyopic subjects and using ROC curve the best cut off point, sensitivity, specificity values were established for presbyopic subjects.

### Study design

The study will involve a randomized, prospective, double-blind clinical trial, with both the patient and evaluator being unaware of the treatment assignment. This protocol is according to SPIRIT-Outcomes 2022 Checklist (for combined completion of SPIRIT 2013 and SPIRIT- Outcomes 2022 items) [15].

### Methods: participants, and outcomes

#### Study setting

The Noordidegan eye clinic in Karaj will be the source of participants for this study. In phase one of this project, we modified and adapted the Persian version questionnaire used in a previous study that focused on young adults [16], and proceed to test its reliability and validity for subjects with presbyopia. A preliminary examination will be conducted by optometrist [name], while optometrist [name] will handle the interventions. Patients who meet the inclusion criteria will be invited to participate in the study after the initial examination. The purpose and details of the research will be explained to the patients, and their informed consent will be obtained.

#### Eligibility criteria

For inclusion in the study, participants must meet the following criteria: a CISS score exceeding the cut-off point established in phase 1 using our modified CISS, near and far best corrected visual acuity of 20/20, presence of CI, near exophoria being at least 4 prism diopters greater than distant exophoria, near point of convergence greater than 6 cm, inadequate near-positive fusion as defined by the Convergence Insufficiency Treatment Trial (CITT) study [17], and normal monocular accommodation amplitude as per the Hofstetter formula.

Participants will be excluded from the study if they meet any of the following criteria: dry eye, any form of strabismus or amblyopia, spherical refractive error ≥ 3.50 diopters, astigmatism ≥ 2.50 diopters, history of prism prescription, vision therapy undergone less than five years ago, history of strabismus or refractive error surgery, history of eye trauma, use of any ophthalmic or general medications or drugs that affect ocular accommodation, such as phenylephrine, anticholinergics (mydriatics), carbonic anhydrase inhibitors, antihistamines, morphine and its derivatives, antidepressants, amphetamine, and imipramine, presence of more than one prism of vertical phoria, any mechanical limitations in the eye muscles, ocular muscle paralysis, nystagmus, and any systemic or neurological diseases that affect binocular vision, such as diabetes, myasthenia gravis, Graves’ disease, and multiple sclerosis.

To ensure blinding, participants will be kept unaware of which group they have been assigned to. Those who express interest in participating in the study and meet the eligibility criteria will be asked to sign an informed consent form. The optometrist responsible for recruitment, [name], will carry out the preliminary evaluation after the participant’s score in the modified CISS questionnaire has been determined.

#### Intervention

Three groups will be considered for the intervention. The intervention will be executed by [name] This individual will be the only one with access to the random allocation file and will administer the treatment based on each individual’s random number as specified by the computer program. To generate a list of random numbers, the website www.random.org will be utilized. Consecutive numbers generated by the website, will be assigned randomly to patients in each of the study groups. The optometrist will be blinded to the evaluation outcomes. Each group will receive the treatment assigned by randomization again.

#### Control group procedure

The control group patients will only receive new near glasses with appropriated addition power, as a standard treatment for presbyopia. Additionally, they will perform a form of exercise that involves random and aimless eye movements at home. This placebo eye exercises will be performed at a fixed distance and over a small area, (6 m) with minimal separation (2 cm) of adjacent stimuli to avoid any impact of accommodative and convergence changes with reduction in eye-to-stimulus distances or if inter-stimulus separation is too large. This exercise will not affect the convergence and accommodation system and will be carried out under the supervision of the optometrist.

#### Home vision therapy group procedure

The home vision therapy group will also receive new near glasses with appropriated addition power, as a standard treatment for presbyopia. In addition, they will be given vision therapy exercises with an instruction form of how and the duration of these exercise. These accommodation/ convergence training includes: Voluntary convergence, Bug on string, Eccentric Circles, Jumping vergence, Barrel card, chiastopic fusion, Brock string, push-up training. The patient will perform a variety of exercises during each session, which will occur three times a week for 20 min–10 min before noon and 10 min at night. These exercises must be documented on a specialized form for a duration of two months. The home exercises consist of eight vision therapy exercises, with two exercises to be completed before noon and two at night. Each exercise should be completed for five minutes, meaning that four different exercises should be performed each day. In the following session, the next four exercises should be done. The exercises should be recorded on the instruction form throughout this time. To improve adherence to intervention exercises will be monitored using video communication applications.

#### Prism prescription group procedure

The prism prescription group will be given the same treatment protocol and instructions as the control group. However, near prismatic glasses will be prescribed using the Sheard’s criterion and their appropriated addition power, and the base in prism will be rounded up and evenly distributed between both eyes. Sheard’s criterion is most popular guideline for prism prescription and it demonstrates optimal effectiveness when applied to individuals with exophoric conditions [18]. They will also be instructed to perform random and aimless eye movements, of which will be done at a distance of 6 m and over a 2 cm area, as mentioned previously they will not affect the convergence and accommodation system.

In all groups, if participants have a refractive error for distance vision, they will be provided with two separate pairs of spectacles, one for near use and one for distance use. To ensure regular usage of the near spectacles (with or without prism) throughout the study, adherence will be monitored through video calls and by participants confirming their usage on an instruction form.

#### Outcomes

The primary outcomes we focused on were the improvement in NPC and NPFV measures at break and recovery points, and the secondary outcomes were improvements in Convergence Insufficiency Symptom Survey (CISS) score, vergence facility, near heterophoria, stereopsis, prism adaptation, NNFV, that will be assessed before and after the intervention and comparison will be done among the groups. These primary and secondary goals are directly related to objective and subjective aspects of convergence insufficiency respectively.

#### Participant timeline

For all the groups after confirmation, all the prescribed glasses will be inspected and utilized, and the patients will not be aware of the group to which they belong. The vision therapy, aimless eye movements and utilization of the glasses will persist for a duration of two months. The follow ups will occur one and two months after the start of the treatment. Optometrist [name] will carry out all optometric exams once again. Figure 1 shows schedule of the study.

**Fig. 1 Fig1:**
[figure not shown]
The predicted participant timeline of enrolment, interventions, and assessments

#### Safety assessment

Every unfavorable incident will be documented and sorted based on whether they are linked to the intervention. Any events that may be expected due to the assumed treatment mechanism, such as nausea, headache, and diplopia will be recorded. However, they have not been observed in previous studies.

Figure 2 provides a flowchart outlining various stages involved in of the study.

**Fig. 2 Fig2:**
[figure not shown]
Flow chart of the study

#### Sample size calculation

To calculate the appropriate sample size for all outcome variables specially those related to primary outcomes, a two-tailed test with α = 5% and β = 10% and 90% power was conducted using the Power Analysis & Sample Size software (PASS, version 11). The selection of appropriate statistics for the sample size determination was based on three previous studies [10, 12, 13]. The sample size in each group was determined using the One-way ANOVA menu of PASS 21 software, taking into account the quantitative nature of the dependent variables and the presence of three groups. The test was conducted with a first type error (α) of 0.05 and a second type error (β) of 0.1, corresponding to a test power of 90%. The mean values of 17 cm, 16 cm, and 21.52 cm, along with a standard deviation of 7.50, were extracted for NPC, and the effect size was calculated as 0.311. Considering a 15% dropout rate, the total number of samples in each group amounted to 50, resulting in a combined total of 150 samples.

### Sample recruitment

#### Methods: assignment of interventions (for controlled trials)

To allocate patients to the randomized treatment groups, the patients will be categorized based on their age, gender, and the severity of their CI using random blocks. We will have 3 groups: control group, prism prescription group, and home vision therapy group. To generate a list of random numbers, the website www.random.org will be utilized. Consecutive numbers generated by the website (ranging from 1 to 150) will be assigned randomly to patients in each of the group by optometrist [name], who has no prior knowledge of the random numbers list. The optometrist responsible for intervention, [name], will be the only person who has access to the random numbers list. Due to the nature of vision therapy and other training instructions provided to the subjects, this optometrist will not be blinded. So participants get assigned consecutive numbers and then the randomized assigns treatments to each number. 1 optometrist applies the treatment. The other masked optometrist makes the measurements. Consequently, the allocation concealment will be ensured because the optometrist in charge of recruitment will be unaware of the group to which the subject will be assigned.

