#### Statistical methods

Analysis will undergo using the Statistical Package for the Social Sciences software (SPSS version, 22). The significance levels of α and β will be set at 5% and 10%, respectively, while the confidence interval will be established at 95%. To compare the research variables before and after the intervention, the paired t-test or its non-parametric equivalent will be utilized. The normality of the data will be checked using the Kolmogorov- Smirnov test. One-way ANOVA with Tukey’s post hoc test will be employed to compare the quantitative variables in the study. ANCOVA will be used to eliminate any intervening variables. The Kruskal-Wallis and Mann-Whitney tests will be used to evaluate groups of quantitative variables in non-parametric conditions. For within-group analysis, repeated measures ANOVA will be conducted when initial homogeneity and normality of data are met. If initial homogeneity is established without normality of data distribution, the Friedman test will be used. A linear mixed model adjusted for the baseline variables will be employed when initial homogeneity is not found. Per protocol analysis principles will be applied in the study. Additionally, univariate analysis and multiple regression analysis will be conducted to identify the predictor factors that influence prism effectiveness in presbyopic patients.

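### Allocation is said to be blocked by age, gender and CI severity, but no arm comparison is committed to those factors and the described 1–150 list shows no strata

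*Protocol article*

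**What the plan says.** **Allocation.** Under Methods: assignment of interventions, the article states that "the patients will be categorized based on their age, gender, and the severity of their CI using random blocks". It gives no cut-points for age or severity and no block size. It then describes the mechanism: "Consecutive numbers generated by the website (ranging from 1 to 150) will be assigned randomly to patients in each of the group", summarised as "So participants get assigned consecutive numbers and then the randomized assigns treatments to each number". The Intervention section repeats the website list, also without strata.

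**Analysis.** The Statistical methods section states: "One-way ANOVA with Tukey’s post hoc test will be employed to compare the quantitative variables in the study". The Sample size calculation section uses the same one-way model. Two further sentences in Statistical methods concern adjustment:

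- "ANCOVA will be used to eliminate any intervening variables". No covariate is named, and nothing says whether ANOVA or ANCOVA decides the arm comparison.
- "A linear mixed model adjusted for the baseline variables will be employed when initial homogeneity is not found". This follows the sentences on within-group analysis, and its use depends on the observed data.

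None of these sentences names age, gender or CI severity.

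**Status.** The Trial status section reports 121 patients randomised as of 3 October 2023.

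**The concern.** Factors used to balance the arms remove part of the between-arm chance variation. An analysis that omits them leaves their variance in the residual, so its standard errors describe a noisier experiment than the one that was run. If the factors are prognostic, confidence intervals are wider than they need be and precision is given away.

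The conditional mixed model does not cure this. Its trigger is baseline imbalance. Successful stratification tends to remove imbalance on exactly these factors, so the trigger would tend to stay off in the case where adjustment is most clearly warranted.

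The allocation text adds a second problem. It claims blocking by three factors and then describes a procedure in which treatment depends only on a consecutive number. A reader cannot tell which scheme was used, and so cannot tell whether the unadjusted analysis is conservative or merely less precise than it could be.

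**Working it through.** **1. The plan's own figure.** Inputs from Sample size calculation: NPC means 17, 16 and 21.52 cm, SD 7.50, α = 0.05, power 90%, dropout 15%, 50 per arm.

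- Grand mean = 54.52/3 = 18.173. Squared deviations are 1.377, 4.723 and 11.200, with mean 5.767 and root 2.401.
- f = 2.401/7.50 = 0.320.
- Non-central F with λ = N·f² needs 43 per arm (power 0.906).
- 43 × 1.15 = 49.5, so 50. 43/0.85 = 50.6, so 51. The stated 50 per arm is reproduced.

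The stated f of 0.311 is slightly below 0.320 and used directly would need 45 completers per arm. That is a separate matter. What counts here is that the sizing model has no stratum or covariate term.

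**2. Direction of the error under stratified allocation.** Let R² be the share of outcome variance explained by the three factors. The documents give no value, so a range is shown. With arms balanced on the factors, the variance of an arm contrast is proportional to 1 − R², while the one-way ANOVA residual still estimates the full variance. The standard error is therefore too large by 1/√(1 − R²), which is 1.054, 1.118 and 1.195 at R² = 0.1, 0.2 and 0.3.

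For the three-group F test (2 numerator degrees of freedom, large sample, perfect balance), the actual error is about α^(1/(1 − R²)):

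- 0.05^1.111 = 3.6%
- 0.05^1.25 = 2.4%
- 0.05^1.429 = 1.4%

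**3. Simulation of the F test itself.** Assumptions: 43 completers per arm, three two-level factors giving 2 × 2 × 2 = 8 strata, permuted blocks of 3 within stratum, and power at f = 0.311. There were 6,000 null runs and 3,000 power runs per cell.

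| Assumed R² | Actual α, one-way ANOVA | Actual α, stratum-adjusted | Power, one-way ANOVA | Power, stratum-adjusted |
|---|---|---|---|---|
| 0 | 5.0% | 4.8% | 0.895 | 0.883 |
| 0.1 | 3.5% | 5.4% | 0.902 | 0.927 |
| 0.2 | 2.2% | 4.7% | 0.908 | 0.954 |
| 0.3 | 1.7% | 4.5% | 0.905 | 0.971 |
| 0.5 | 0.3% | 5.3% | 0.940 | 0.998 |

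Simulation standard errors are about √(0.05 × 0.95/6000) = 0.3 percentage points for α and √(0.9 × 0.1/3000) = 0.005 for power. The simulated α agrees with step 2 in direction and roughly in size.

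Unadjusted power stays near 0.90 because the arm means themselves vary less under stratification, which offsets the oversized standard error. At R² = 0 the adjusted model is 0.012 lower, about 1.5 standard errors of that difference (0.008).

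**4. If the list is unstratified.** The factors then vary by chance between arms, their variance properly belongs in the residual, and one-way ANOVA keeps its nominal α. Adjustment still gains precision when the factors are prognostic.

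**5. Claim against mechanism.** The stated blocking needs an allocation sequence that depends on a participant's stratum. The described step links treatment to a consecutive number from one run of 150, and no stratum enters it.

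**The case against.** Several points against the concern are sound.

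- A reader might infer that the plan contains no adjustment at all. It does not support that: ANCOVA and a baseline-adjusted mixed model are both mentioned, and no test is labelled primary. What stands is narrower. The covariates are unnamed and the mixed model is conditional on the data. Naming covariates can be left to an analysis plan, but the article goes further than silence: it names the arm comparison and fixes a data-dependent trigger.
- A reader might infer that a 1–150 list cannot deliver stratification. It could, if sectioned by stratum, and a condensed article may omit that detail. The supportable statement is that the mechanism as described shows no strata and does not match the sentence before it.
- A reader might infer inflated false positives or a trial that misses its planned power. Neither follows. Under stratification the unadjusted test is conservative, and its simulated power is about 0.90 or higher. The loss is relative to an adjusted model only.
- The two harms are alternatives. If the list is unstratified, the standard errors are not too large. If allocation is stratified, the fault in the randomisation text is one of description.
- CI severity is not a defined variable in Table 1 or Table 2. Those tables give age, gender, CI by the CITT definition and its component measures. Adjustment therefore needs a definition first, and severity may coincide with the baseline value of a primary outcome.

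**Conclusion.** The concern holds in limited form. The article claims allocation blocked by three factors, names an arm comparison that omits them, and commits no analysis to them. If allocation is stratified and the factors explain 10/20/30% of outcome variance, the actual error of the one-way ANOVA is about 3.5/2.2/1.7% instead of 5%, and power is about 0.90 where an adjusted model would reach 0.93/0.95/0.97. These figures rest on an assumed R², 8 strata, blocks of 3 and 43 completers per arm; only the design inputs come from the document. Inference stays valid in either case, so this is lost efficiency plus an allocation description that must be reconciled.

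**What to change.** 1. Make ANCOVA the primary arm comparison, with age, gender and CI severity as prespecified fixed covariates regardless of any baseline test. Apply the pairwise multiplicity adjustment to the adjusted means.
2. Define CI severity as the baseline measure used for allocation. Where that measure is the baseline value of the outcome being analysed, enter it once.
3. State which allocation scheme was used for the 121 participants already randomised. If it was stratified, give the strata and say how the numbered list was divided among them. If it was one unstratified list, delete the stratified-block claim and keep the covariates for precision.

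Cost: wording, a definition of severity, and a few degrees of freedom. With 43 per arm the residual has 129 − 3 = 126; three single-degree covariates leave 123, and full eight-stratum adjustment leaves 129 − 10 = 119. If the factors are not prognostic, a slight power loss is possible (0.883 against 0.895 in the eight-stratum simulation). No change in sample size is needed.
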